### Study Design

This is an 18-month, prospective, multicenter, open-label study with 3 parallel arms, using randomization and control to assess a range of oral health and dental esthetic metrics (Figure 1). The primary objective is to compare these metrics between cigarette smokers transitioning to C-F NA and those who continue smoking.

Eligible smokers will be allocated randomly to either the control group (arm A), which will receive standard care inclusive of cessation counseling (ie, very brief advice [VBA]) or the intervention group (arm B), which will be given a C-F NA of their choice and will also receive VBA. Individuals who have never smoked will form a reference group (arm C). Throughout the study, participants from all 3 groups will undergo regular assessments of their oral health and dental esthetic. The study will be conducted in 4 dental clinics across 4 different countries (Italy, Poland, Moldova, and Indonesia).

The study protocol adheres to the guidelines stipulated by the Standard Protocol Items: Recommendations for Interventional Trials (SPIRIT) guidelines.

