**Figure 2 figure2:**
[figure not shown]
Study flow diagram of study participants. C-F NA: combustion-free nicotine alternatives.

Screening visits will be performed within 28 days before enrollment to verify the eligibility criteria (visit 0; Figure 2). During the screening visit, sociodemographic data, medical and oral health history, detailed information about nicotine and tobacco consumption, and interest in trying C-F NA will be recorded. Screening for periodontal disease will be performed to exclude periodontitis, as per the definition of the guidelines of the 2017 Classification of Periodontal and Peri-implant Diseases and Conditions [28]. Smokers will be offered a smoking cessation program as per local guidelines. Any smokers who express the intention of booking for the cessation program or to quit smoking in the next 6 months will be urged to do so and will not be recruited in the study. Participants taking part in the study will be informed that they are free to quit smoking and withdraw from the study at any time. Moreover, smokers will be encouraged to quit smoking at every contact throughout the study.

Within 28 days of the screening visit, eligible participants will be invited to attend an enrollment visit (visit 0). Inclusion and exclusion criteria will be verified again. Smokers will be reminded of the risks associated with smoking before enrollment in the study and that they are free to voluntarily quit smoking and nicotine or withdraw from the study at any time. All participants will undergo a series of measurements (Tables 1-3) followed by dental scaling and polishing procedures to remove calculus, plaque, and stain.

Smokers not intending to quit will then be randomly assigned to either the control (arm A) or the intervention (arm B) group. The randomization sequence will be generated by a computer, with an allocation ratio of 1:4 (arm A: arm B) to accommodate for the estimated 25% proportion of participants achieving a sustained reduction in cigarette consumption of at least 90% in arm B (as detailed in the Statistical Considerations section). Smokers in the control group (arm A) will receive standard care, inclusive of cessation counseling (ie, VBA) at each study visit. Smokers in the intervention group (arm B) will have the option to try and choose a preferred C-F NA (ECs and HTPs) from a given pool of popular options present in the respective markets and will also receive VBA.

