Individuals who have never smoked will be allocated to the reference group (arm C). Never smokers in the reference group will serve as comparators for assessing any background changes in the primary study end point (ie, Modified Gingival Index [MGI]) that may occur over time. Although never smokers will not undergo randomization, efforts will be made to achieve a comparable distribution of sex and age across all study arms.

The trial is designed as an unblinded trial because of the nature of the intervention, where participants and trial staff cannot be blinded to the specific intervention being provided. However, data analyses will be conducted blind to study arms allocation. All other trial staff who have access to outcome data will remain blinded until prespecified data analyses will be completed.

Baseline measurements will be performed at visit 1 (baseline visit) and 14 days after scaling and polishing procedures at enrollment (visit 0). Study measurements will include MGI assessment, plaque imaging, dental shade quantitation, tooth stain scores, and oral health–related quality of life questionnaires (Tables 1-3).

Smokers in arm B will be provided with a C-F NA of their choice. They will receive training and counseling on how to use the chosen C-F NA and will be provided with a full 2-week supply of the required consumables (cartridges or pods or e-liquid refill bottles for ECs and tobacco sticks for HTPs). Participants wishing to use an HTP will receive one kit and a supply of tobacco sticks of their choice. They will receive the number of tobacco sticks per day corresponding to the number of cigarettes smoked per day at baseline. Participants wishing to use a vaping product will receive one vaping kit and a supply of e-liquids of their choice. Products will be supplied at each subsequent visit throughout the study according to the study product supply schedule in Table 4.

After the baseline visit, participants will be invited to attend 4 more clinical visits (visits 2-5) to repeat study measurements (Tables 1-3).

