### Study Measurements and Calibration

A detailed description of the study measurements that will be specifically carried out at the dental clinic is provided in Multimedia Appendix 2.

All assessors will be trained on MGI scoring, tooth stain assessment, and the correct use of technologies and software used to quantify dental plaque, tooth discoloration, exhaled carbon monoxide monitoring, and electronic case report form (eCRF) use. Assessors will be periodically calibrated on MGI scoring and tooth stain assessment. To ensure consistency in the measurements, the same assessor will collect all study end points in the same participant over the entire study period.

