A generalized linear regression model will be used to adjust for all identified confounders. To identify possible predictors of primary and secondary study end points, a regression model will be estimated in which each study end point will be entered as the dependent variable. Possible predictors will be entered into the model as independent variables (including study group; age; gender; cigarette consumption; combustion-free nicotine delivery systems use; and frequency of personal oral hygiene, eg, tooth brushing, mouth washing, and dental flossing frequency) to assess the interactions. Following the results obtained from each regression model, comparisons between and within study groups will be performed using analysis of covariance adjusted for age, gender, and frequency of personal oral hygiene followed by the Tukey post hoc comparison test.

The goal of our study is to help smokers abstain from cigarette smoking to assess changes in oral health regardless of the product used. This study is not designed to compare the efficacy between HTPs and ECs in terms of smoking cessation. Nonetheless, we will consider a secondary analysis that takes into account the potential different impact of HTPs versus ECs in terms of oral health outcomes.

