The study design incorporates several significant and groundbreaking characteristics. First, we aim to enhance adherence to C-F NA and optimize overall compliance with the study’s instructions through the provision of a diverse range of products, encompassing the most popular options available in the market. This approach allows participants to tailor their own gratifying “nicotine experience” by selecting the C-F NA that aligns with their preferences. By doing so, we anticipate not only fostering a transition to the latest technology but also facilitating the reduction of cigarette smoking and bolstering long-term prevention of relapse [38-42]. It is worth highlighting that this aspect of personal choice is notably absent in studies of harm reduction. Furthermore, it is important to emphasize that the outcomes of this research will not be product specific, thereby minimizing constraints on generalizability.

Second, the study is being run in many different locations across the globe and so the challenge was to find a primary end point that could be measured by different operators in different sites, using a standardized measurement system that has been used previously and so has provenance. The index to be used had to be simple, reproducible, and relatively easy to compare between different sites and different operators. Ideally, the assessors should be able to calibrate the index to be used and compare the calibration results. The MGI is a widely used industry-standard index to determine changes in the gingival health of volunteers in clinical studies [29,43,44]. This index is simple, noninvasive, and reproducible, and it is hoped that it will be possible to train different examiners in different locations to align their assessments, thus making the results comparable. As the MGI is noninvasive, there is no gingival probing, and it is thought to be easier to calibrate examiners and compare kappa scores. Although subjective in nature, the lack of probing removes one of the variables present in using pressure to probe the gingivae. It is also thought to afford greater sensitivity in determining therapeutic efficacy [45]. This study will be the first to investigate the long-term impact of smoking or C-F NA intervention on MGI.

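### Centre is missing from the ANCOVA covariates and the secondary between-arm tests, so if centre shares are unequal, country differences in change can pass for never-smoker or product effects

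*Protocol article*

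**What the plan says.** All points are from the Protocol article.

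- **Adjusted models (Statistical Analyses).** For the regression: "Possible predictors will be entered into the model as independent variables (including study group; age; gender; cigarette consumption; combustion-free nicotine delivery systems use"; the list ends with oral hygiene frequency. The ANCOVA used for between-group and within-group comparisons has three covariates: age, gender and oral hygiene frequency. Tukey comparisons follow.
- **Secondary end points (same section).** Arms are compared by t test or Mann-Whitney test, without covariates.
- **Where centre appears (same section).** Only the mixed model listed for the primary end point contains it, as random centre and arm-by-centre factors.
- **Sites (Study Design).** "The study will be conducted in 4 dental clinics across 4 different countries (Italy, Poland, Moldova, and Indonesia". Centre and country therefore coincide.
- **Arm C (Study Design, after Figure 2).** Never smokers are not randomised; "efforts will be made to achieve a comparable distribution of sex and age across all study arms". Centre is not mentioned there.
- **Product (Study Design, after Figure 2).** Arm B participants choose an e-cigarette (EC) or heated tobacco product (HTP) "from a given pool of popular options present in the respective markets".
- **Product comparison (Statistical Analyses).** "we will consider a secondary analysis that takes into account the potential different impact of HTPs versus ECs". No model is given.
- **Assessors.** Study Measurements and Calibration provides for training, periodic calibration, and that "the same assessor will collect all study end points in the same participant over the entire study period". The Discussion says the challenge was to find "a primary end point that could be measured by different operators in different sites".

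**The concern.** For arm A against arm B, randomisation prevents systematic confounding with centre, and the primary mixed model contains centre as well. Neither protection reaches two other contrasts.

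- **Arm C against arms A and B.** Arm C is recruited, not randomised, and the stated balancing effort covers sex and age only. If its spread over the four clinics differs from that of the smokers, the contrast takes in differences between countries.
- **HTP against EC.** Choice is personal and the range on offer depends on the national market, so product use is likely to vary with country.

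What would leak into these contrasts is any between-country difference in change from baseline: examiner drift, different use of the scale, and local habits or care. The Discussion itself names diet and alcohol as factors that can significantly affect the assessments, and neither is a listed covariate. Adjusting for age, gender and hygiene frequency does not remove such differences. At stake is a country difference reported as a never-smoker or product effect.

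**Working it through.** **Inputs from the Protocol article (Sample Size Calculation).** Design difference 0.10, SD 0.21, one-sided 5%, 90% power, 77 per group; arms of 92, 368 and 40; dropout 20%.

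**Plan's own figure.** A one-sided two-sample t test with the noncentral t distribution gives 77 per group, and all 15 cells of Table 5 reproduce. The design difference and SD are therefore sound as a yardstick; the point does not depend on the sample size.

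**Assumed inputs.** The documents give no centre effects, no arm C counts by centre and no product shares. I assume that centre means of MGI change vary with SD s = 0.05 to 0.10. If 0.21 is the total SD, this puts 0.05²/0.21² = 6% to 0.10²/0.21² = 23% of the variance between centres, so the upper end is a strong assumption.

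**Arm C against arms A and B.** With arms A and B spread evenly over four centres and arm C having centre shares w, typical bias = s × √Σ(w − 0.25)².

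| Arm C shares | √Σ(w − 0.25)² | s = 0.05 | s = 0.10 |
|---|---|---|---|
| 25/25/25/25 | 0 | 0 | 0 |
| 40/30/20/10 | √0.05 = 0.224 | 0.011 | 0.022 |
| 50/50/0/0 | √0.25 = 0.5 | 0.025 | 0.050 |
| 100/0/0/0 | √0.75 = 0.866 | 0.043 | 0.087 |

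Error rate under a related assumption: two centres differ from the other two by D = 0.10 in mean change and each pair holds half of arm B. With share p of arm C in the first pair:

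- Bias = D × (p − 0.5).
- Total SD = √(0.21² + 0.10²/4) = 0.216.
- Standard error for 40 against 368 = 0.216 × √(1/40 + 1/368) = 0.036.
- For p = 0.60, 0.75 and 1.00 the bias is 0.010, 0.025 and 0.050. The two-sided 5% test then rejects in 6%, 11% and 29% of trials with no true difference. For p = 0.50 the bias is 0 and the rate is 5%.

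These rates use recruited numbers; with dropout the excess over 5% is somewhat smaller.

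**HTP against EC.** HTP and EC users together make up arm B, so both groups shift. The weights are the differences in centre share between the two user groups: typical bias = s × √Σ(w_HTP − w_EC)². With four equal centres:

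- HTP share 70% in two centres and 30% in the other two: HTP users split 35/35/15/15 and EC users 15/15/35/35; √(4 × 0.20²) = 0.4, so bias 0.020 to 0.040.
- HTP only in two centres, EC only in the other two: √(4 × 0.5²) = 1.0, so 0.050 to 0.100.
- HTP only in one centre, EC only in the other three: √(1 + 3 × (1/3)²) = 1.155, so 0.058 to 0.115.

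**Effect of adding centre.** A 2,000-run simulation with no true product effect used 296 arm B completers (74 per centre, close to 368 × 0.8 = 294), D = 0.10, HTP share 70% against 30%, and SD 0.21.

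| Model | Mean HTP − EC difference | Rejections at 5% |
|---|---|---|
| Without centre | 0.040 | 37% |
| With centre as fixed factor | 0.000 | 5.1% |

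**The case against.** The case against is substantial, and several of its points stand.

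- **The regression list is open.** It is introduced as non-exhaustive, and the section says the model will adjust for all identified confounders. A reader might infer that centre is excluded from the regression; the text does not say so. The ANCOVA list, however, has three named covariates and no such opening.
- **Examiner alignment is planned.** The Discussion says "it is hoped that it will be possible to train different examiners in different locations to align their assessments", from which a reader might infer that alignment is left to hope. Study Measurements and Calibration and the later Discussion commit to training and calibration. Because one assessor follows each participant, a constant examiner offset cancels in change from baseline. Drift, differing scale use and real country trends do not cancel, nor do offsets in any comparison of levels. Shade and plaque are measured by instrument, so scoring differences bear mainly on MGI and tooth stain.
- **Arm C is not shown to be concentrated anywhere.** A reader might infer that it is tied to particular clinics; nothing in the document says so. With equal shares the bias is zero.
- **The product comparison is only under consideration.** With no model stated, it cannot be called wrongly specified. The point there is preventive.
- **Details belong in the analysis plan.** That is fair for unstated details. Here the ANCOVA covariates are stated, without centre.

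**Conclusion.** The point holds in limited form. As written, the ANCOVA and the unadjusted secondary tests leave contrasts with arm C open to confounding by country, and any product comparison would be open to it too unless centre is included. The primary comparison of arm A with arm B has a model with centre, so this point does not support a reading that the primary result is compromised.

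The size cannot be known from the documents. It is nil if centre shares are equal, small for a moderate imbalance, and close to the planned difference of 0.10 only where arm C comes from a single centre and s is at the top of the assumed range. For HTP against EC the same assumptions give larger values when products separate by country. All these figures rest on the assumed between-centre variation and the illustrated shares. The change is worth making because it costs little and does not depend on which scenario is true.

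**What to change.** 1. Name centre as a fixed factor (4 levels, 3 df) in the regression and in the ANCOVA.
2. For secondary between-arm comparisons involving arm C, use that centre-adjusted model in place of the t or Mann-Whitney test. A factor cannot be added to those tests, so this is a change of method.
3. Include centre in any HTP-against-EC analysis, and label the analysis non-randomised and exploratory.
4. Report counts of arm C and of HTP and EC users by centre, so that readers can see whether the shares differ.

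The cost is analysis-plan wording and 3 degrees of freedom among 500 planned participants (92 + 368 + 40). The downside is a wider interval where arm C or a product is concentrated in one centre. If products are fully separated by country, no within-centre product contrast can be estimated, and the report should say so.

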**Methods:**

Regular smokers not intending to quit and without clinical signs of periodontitis will be randomly assigned (1:4 ratio) to either standard of care with brief cessation advice (control group; arm A) or C-F NA use (intervention group; arm B). The study will also include a reference group of never smokers (reference group; arm C). The primary end point is the change in the Modified Gingival Index (MGI) score from baseline between the control arm (arm A) and the intervention arm (arm B) at the 18-month follow-up. In addition, the study will analyze the within- and between-group (arms A, B, and C) changes in MGI assessment, plaque imaging, dental shade quantitation, tooth stain scores, and oral health–related quality of life questionnaires measured at each study time point. All participants will attend a total of 7 clinic visits: screening, enrollment, and randomization (visit 0); baseline visit—day 14 (visit 1); day 90 (visit 2); day 180 (visit 3); day 360 (visit 4); and day 540 (visit 5). This multicenter study will be conducted in 4 dental clinics in 4 countries. The statistical analysis will involve descriptive statistics for continuous and categorical data. Primary end points will undergo tests for normality and, based on distribution, either a 2-sided *t* test or Mann-Whitney *U* test. Linear mixed model with random factors center and study arms by center will also be applied. Secondary end points, including MGI assessment and quality of life, will be subjected to similar tests and comparisons. Only if one value of the parameter MGI is missing after day 1, the last available observation will be carried forward. The analysis will be performed on the substituted data. Secondary parameters will not have missing value replacement.

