### Statistical Considerations

#### Sample Size Calculation

For a valid sample size calculation, literature research was performed for the primary end point of the study (ie, MGI). Unfortunately, no data were available for such a study. However, data from studies with mouth rinse were available, and based on these studies [30,31], a mean MGI change of 0.08 with an SD of 0.18 of the MGI seemed relevant.

However, in these studies, higher mean MGI changes were observed because active treatment was administered, which was not the case in this study. Thus, several scenarios with different mean MGI changes and SDs will be applied.

The following hypotheses will be tested with a 1-sided independent *t* test:

H0: µA≤µB versus H1: µA>µB

where µA denotes the mean change MGI from baseline to after 18 months of regular smoking and µB denotes the mean MGI from baseline to after 18 months of C-F NA use.

For sample size calculation, SAS software (version 9.4; SAS Institute) was used and several scenarios were applied, assuming that the data are normally distributed. The results are summarized in Table 5, which presents the calculated sample sizes for the comparison of µA versus µB by a 1-sided independent *t* test, a significance level of 5%, and a power of 90%, depending on the expected MGI change and SD.

As no active treatment is given in this study, a lower effect than the observed values needs to be assumed. Therefore, a mean MGI change of 0.1 with an SD of 0.21 was chosen. Hence, a sample size of 77 patients per treatment group is required. Considering a dropout rate of 20% over 2 years’ observation phase [32,33], a sample size of at least 92 per treatment group is required. In addition, it is estimated that approximately 25% of those switching to C-F NA use will abstain or substantially (≥90%) reduce smoking [34], and only these participants deliver valid results. Therefore, 4 times more participants should be recruited in the C-F NA group (4 × 92 = 368). This results in a total sample size of 460 (92 in arm A+368 in arm B).

In arm C, we have determined a sample size of 40, empirically with no formal statistical analysis, as this cohort’s primary study end point (ie, MGI) is expected to be stable throughout the study.

**Table 5 table5:** Summary table including the sample size for each arm of the study depending on the mean Modified Gingival Index (MGI) change and SD.

Nominal power	Mean MGI change	SD^a^				
		0.20	0.21	0.22	0.23	0.24

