#### Statistical Analyses

Statistical methods used in the analysis of this study will include descriptive statistics with the descriptive presentation of the total sample value, mean, SD, median, minimum, maximum, and 95% CIs for (pseudo) continuous data and categorical data. Further evaluations will be summarized in tables by counts and percentage of scores.

Statistical methods for primary study end points will include the following: the Shapiro-Wilk test of normality on calculated values (in case of normal distribution, a 2-sided independent *t* test and in case of nonnormal distribution: a 2-sided Mann-Whitney *U* test) and a linear mixed model with the random factors “center” and “study arms by center.”

Designated as study arm C, the never-smoker group will establish a baseline reference for the oral health parameters. This group is anticipated to provide insights into the underlying changes in the primary study end point (MGI) that may emerge over time in individuals who have never smoked.

Statistical methods for secondary study end points will include the following: for comparisons of each study arm for parameters such as MGI assessment, plaque imaging, dental shade quantitation, tooth stains scores, and oral health–related quality of life questionnaires, the Shapiro-Wilk test of normality on calculated values (in case of normal distribution, a 2-sided independent *t* test and in case of nonnormal distribution: a 2-sided Mann-Whitney *U* test); for comparisons of each assessment time for parameters such as MGI assessment, plaque imaging, dental shade quantitation, tooth stains scores, and oral health–related quality of life questionnaires, the Shapiro-Wilk test of normality on calculated values (in case of normal distribution, a 2-sided independent *t* test and in case of nonnormal distribution: a 2-sided Mann-Whitney *U* test); accounting for missing, unused, and spurious data.

If only one value of the parameter MGI is missing after day 1, the last available observation will be carried forward. The analysis will be performed on the substituted data. For secondary parameters, no replacement of missing values will be applied.

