Fourth, maximizing the magnitude of observable changes at the study end points is critically important. Given that several factors (including duration of smoking exposure, variations in oral hygiene practices, type of diet, and level of alcohol consumption) can significantly affect assessments of gum health and dental esthetics, we reduced baseline variability by using data obtained after the visit during which scaling and polishing was carried out. By removing dental plaque, calculus, and stains, we provide all study participants with the best possible oral health status (gum health and teeth appearance) at the beginning of the study. Considering that a 14-day interval is generally required to allow gingival restoration from tissue trauma caused by scaling and polishing [51], measurements that will be considered for this normalized baseline will be obtained 14 days after scaling and polishing. Any progressive change in gum health or tooth appearance will be compared with the reference data of this baseline. In addition to the inclusion of a full scale and polish at the beginning of the study in an attempt to maximize the magnitude of observable changes of study end points, it is also important to consider that the length of the study is adequate and that the study population will have to be one that allows the possibility of measuring such a change. Although the long-term impact of smoking and smoking cessation on gingival health and tooth appearance has never been investigated in a prospective trial, the planned 18 months duration of the study is deemed to be adequate for the detection of significant changes in study end points. Chronic periodontal disease is common in smokers and is an irreversible condition that may stabilize with active treatment [52]; however, it is unlikely to improve with the simple measure of smoking cessation alone. Therefore, participants with periodontitis will be excluded and only participants with mild to moderate gingivitis will be recruited, as they are more likely to show measurable changes in study end points with continuing to smoke, smoking cessation, or the use of C-F NA.

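### No analysis the article names for MGI adjusts for baseline MGI; the unadjusted change-score test is valid but may be less precise, by an amount the article's figures cannot settle

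*Protocol article*

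**What the plan says.** The Abstract (Methods) defines the outcome as a change score at 18 months, compared between arms A and B: "The primary end point is the change in the Modified Gingival Index (MGI) score from baseline between the control arm (arm A) and the intervention" (the sentence goes on to name arm B). Under Statistical Analyses, a Shapiro-Wilk test selects the comparison: "in case of normal distribution, a 2-sided independent" t test, otherwise a 2-sided Mann-Whitney U test. Neither takes covariates. The section adds "a linear mixed model with the random factors" for center and for study arm by center, and does not write out its fixed effects.

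Three further analyses follow in the same section:

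- a generalized linear regression for whatever confounders are identified, none of them named;
- a predictor regression whose list is introduced as inclusive and contains study group, age, gender, cigarette consumption, product use and oral hygiene frequency;
- an "analysis of covariance adjusted for age, gender, and frequency of personal oral hygiene followed by the Tukey post hoc comparison test".

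Only the third list is closed. Baseline MGI appears by name in none of the analyses. Tables 1 to 3 schedule MGI at V0 and V1 in all three arms. Baseline is V1, 14 days after scaling and polishing. The Discussion (Overview, fourth feature) explains this choice: "we reduced baseline variability by using data obtained after the visit during which scaling and polishing was carried out".

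**The concern.** A change score uses the baseline value by subtraction, which fixes its coefficient at 1. If the true slope of V5 MGI on V1 MGI differs from 1, a chance baseline difference between the arms is not removed correctly in the trial at hand, and the residual variance is larger than it needs to be. The authors chose to adjust one set of comparisons and wrote out the covariates, but left out the outcome's own baseline value, which is usually a natural first candidate. What is at stake is the width of the confidence interval for A minus B. This deserves attention because the trial was sized 1-sided while the analysis is 2-sided, and because enrollment is complete, so precision can no longer be gained by adding participants.

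**Working it through.** **Inputs from the article (Sample Size Calculation).** "a mean MGI change of 0.1 with an SD of 0.21 was chosen"; "a significance level of 5%, and a power of 90" percent; 77 per group before dropout, 92 after; 368 in arm B. The sizing test: "The following hypotheses will be tested with a 1-sided independent" t test. I take 0.21 as the SD of the change score.

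**Inputs assumed.** The correlation r between V1 and V5 MGI, and the ratio L = SD(V5)/SD(V1). The article gives neither, so a range is shown.

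**1. The plan's own figure.** Exact noncentral-t power, difference 0.10, SD 0.21, 1-sided 5%: 77 per group gives 90.3%, and 77 is the smallest number reaching 90%. The stated figure reproduces, as do all 15 cells of Table 5.

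**2. The planned test.** The same inputs with a 2-sided 5% test give 83.5%. The drop from 90.3% comes entirely from the change of sidedness, not from the missing covariate.

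**3. Variance with and without adjustment.** Set SD(V1) = 1.

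- Change score: 1 + L² − 2rL
- Adjusted for V1 MGI: L²(1 − r²)
- Ratio, adjusted to change: L²(1 − r²) / (1 + L² − 2rL)

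The change-score variance minus the adjusted variance is 1 − 2rL + r²L² = (1 − rL)². This is never negative, so the ratio never exceeds 1. It is zero exactly when the slope rL equals 1. When L = 1 the ratio reduces to (1 + r)/2.

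**4. Power at 77 per group, 2-sided 5%.** The adjusted SD is 0.21 × √ratio; unadjusted power is 83.5%.

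| L | r | Slope rL | Variance ratio | Adjusted SD | Power |
|---|---|---|---|---|---|
| 1 | 0.3 | 0.30 | 0.650 | 0.169 | 95.4% |
| 1 | 0.5 | 0.50 | 0.750 | 0.182 | 92.4% |
| 1 | 0.7 | 0.70 | 0.850 | 0.194 | 89.0% |
| 1.25 | 0.3 | 0.375 | 0.784 | 0.186 | 91.2% |
| 1.25 | 0.5 | 0.625 | 0.893 | 0.198 | 87.4% |
| 1.25 | 0.7 | 0.875 | 0.981 | 0.208 | 84.2% |
| 1.5 | 0.3 | 0.45 | 0.871 | 0.196 | 88.2% |
| 1.5 | 0.5 | 0.75 | 0.964 | 0.206 | 84.8% |
| 1.5 | 0.7 | 1.05 | 0.998 | 0.210 | 83.6% |
| 2 | 0.5 | 1.00 | 1.000 | 0.210 | 83.5% |

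One case worked through, L = 1.5 and r = 0.5: 2.25 × 0.75 / (1 + 2.25 − 1.5) = 1.6875 / 1.75 = 0.964.

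**5. What 77 per group represents.** The article expects about 25% of arm B to stop or nearly stop smoking and counts only those as informative, so 77 against 77 describes a comparison limited to arm B switchers. With all randomised participants and 20% dropout, the numbers are 92 × 0.8 ≈ 74 and 368 × 0.8 ≈ 294. If the 0.10 difference held across all of arm B, unadjusted 2-sided power would be 95.5%.

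**The case against.** The best defence has four parts.

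**The change-score test is legitimate.** It already uses the baseline, and randomisation makes it unbiased with a valid confidence interval. This stands.

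**Most model specifications are open.** The confounder regression, the predictor list and the mixed model's fixed effects could all take baseline MGI in a fuller plan. A reader might infer that the plan excludes baseline adjustment throughout; the article does not support that. It does support a narrower statement: the primary test takes no covariates, and the ANCOVA list is closed without baseline MGI. That ANCOVA serves later between- and within-group comparisons rather than the primary test.

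**The gain may be small.** A reader might infer from the scaling and polishing step that the slope is well below 1 and the gain therefore large. This does not follow. The slope is r × SD(V5)/SD(V1), so for a given r a smaller V1 spread raises it. The reset might also lower r, but the article reports neither quantity. The equal-SD rows are thus a favourable scenario for a plan that sets out to shrink baseline variability.

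**The power shortfall has another source.** Attributing the gap between 83.5% and 90% to the missing covariate would be wrong; it is a 1-sided and 2-sided mismatch.

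What remains is a named method that leaves out a collected value which, apart from one degree of freedom, cannot increase the residual variance and may reduce it usefully.

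**Conclusion.** The point holds as a matter of efficiency. No analysis named in the article adjusts for baseline MGI, and the only closed covariate list omits it. This is neither bias nor a sample-size error: 77 is right for the 1-sided unadjusted test it was computed for. In the scenarios tabulated, 2-sided power at 77 per group after adjustment runs from 83.5% (no gain) to about 95%. These figures rest on an assumed r and L, on 0.21 being the SD of change, on a linear V1-V5 relation, and on a comparison restricted to switchers in arm B. With about 74 against 294 and the full 0.10 difference, power is already 95.5% unadjusted, so there the benefit is mainly a narrower interval. I am confident about the omission, but not about the size of the benefit.

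**What to change.** Under Statistical Analyses, make the primary A-versus-B analysis a linear (mixed) model for V5 MGI, or its change from V1, with arm, the center terms and V1 MGI. Add V0 MGI as a further covariate: it is measured before randomisation, whereas V1 falls 14 days after it in an open-label trial, although arm B receives its device only at V1. State in the text which value is the baseline covariate.

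For each secondary end point, add its matching baseline value to the ANCOVA for the randomised A-B contrast. Arm C is not randomised, and baseline adjustment is open to debate there, so report contrasts with arm C with and without the covariate.

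The cost is wording in the analysis plan, fixed before the data are examined by arm, and about one degree of freedom per covariate. Participants, visits and measurements are unchanged.
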